## Abstract

**Background:**

Expectations are considered an important mechanism of change in psychotherapeutic interventions, including internet- and mobile-based interventions (IMI). This study aims to investigate whether two expectation-focused microinterventions can enhance the effects of an IMI for participants with elevated depression.

**Methods:**

All participants will receive an established IMI consisting of six evidence-based cognitive behavioral modules. In this 2×3 factorial design, 720 adult participants will be randomized to receive (1) either the IMI in standard or personalized framing (first randomization factor), in combination with (2) an expectation-focused telephone call mid-treatment, a supportive phone call or no phone call (second randomization factor). The primary outcome is depression at mid- and post-treatment (BDI-II). Secondary measures include expectations, adherence, state and trait anxiety and depression, disability, negative effects, and satisfaction with treatment.

**Discussion:**

This study will increase knowledge about applying micro-interventions to modify expectations and improve the effects of IMI in the treatment of depressive symptoms. Scalable IMI has the potential to improve healthcare but ways to further improve their effects and adherence need to be explored.

**Trial registration:**

The trial was prospectively registered under DRKS00032982. Registered on July 11, 2023.

## Administrative information

Note: the numbers in curly brackets in this protocol refer to SPIRIT checklist item numbers. The order of the items has been modified to group similar items (see http://www.equator-network.org/reporting-guidelines/spirit-2013-statement-defining-standard-protocol-items-for-clinical-trials/).

## Introduction

### Background and rationale {6a}

Depression is a highly prevalent and debilitating disorder [1]. Still, it is undertreated and access to treatment is associated with significant barriers. Internet- and mobile-based interventions (IMIs) offer a low-threshold, flexible, and easy-to-access alternative to more intensive healthcare support. IMIs are self-help interventions based on psychotherapy principles. Meta-analyses on IMIs for depression have reported medium to large effects from pre- to post-treatment [2], with comparable effects to face-to-face therapy [3]. However, traditional psychotherapy and IMIs for depression only achieve response rates of 40–50% [4]. Common side effects of psychotherapy, including increased symptoms, also frequently occur in IMIs [5]. Given the scalability and dissemination potential of IMIs, avenues to enhance their positive effects and reduce their side effects should be explored.

Optimizing expectations about the outcomes of treatments through psychological interventions may improve treatment effects. A recent meta-analysis found a positive association between early outcome expectations and treatment effects in face-to-face therapy as well as IMIs [6]. However, findings on the impact of expectations on outcome in IMIs, specifically for depression, do not yet paint a clear picture: In one study, higher expectations were associated with delayed response to an IMI for depression [7], while in another study, higher expectations predicted response [8]. The negative effect of overly optimistic expectations may be interpreted in light of cognitive prediction errors: Patients with overly optimistic early expectations may experience a discrepancy between expectations and outcomes that may impede their response to treatment (for the discussion of an optimal tipping point for expectation and expectation violation, see also Rief et al. [9]). These findings underline the need to go beyond merely inducing positive expectations, but rather need to optimize and tailor them in a personalized and realistic manner, as overly optimistic expectations may be detrimental to treatment response. Two context-specific microinterventions that have the potential to optimize expectations may be particularly relevant in IMIs: personalization and human support. Personalization is often achieved through individualized guidance but may also entail other aspects, such as tailoring the treatment content, order of content, user interaction, or alerts/reminders [10]. The interconnections between expectations and levels of personalization are not yet understood [10]. Human contact can be powerful in this digital setting, in particular for enhancing adherence rates [11]. This human contact may also present a promising avenue to optimize expectations. For example, information about the potential success of a psychological intervention could be communicated in a warm and competent manner, as this can change negative expectations, whereas simply communicating the potential benefits without a warm and competent manner does not [12].

Given their highly standardized settings, IMIs offer a unique opportunity to study the temporal dynamics and effects of expectations prospectively over longer time frames. Additionally, the IMI setting allows us to disentangle the impact of expectations from other treatment factors. Alliance with the therapist is, for instance, considered a key mechanism of change in psychological interventions. In the context of face-to-face psychotherapy, expectation-optimizing interventions are inherently intertwined with the personal contact to the therapist [13]. As therapeutic contact is limited and can be systematically controlled in IMIs, studying expectations and other treatment factors is highly informative and may provide more insight into the relative contribution of different treatment factors to the outcome, in turn facilitating a tailored intervention of specific mechanisms.

### Objectives {7}

We postulate that (simulated) personalization before initiating an IMI and an expectation-optimizing personal contact at mid-treatment would modify patients’ expectations and improve treatment effects. A factorial design will enable us to disentangle the mechanisms and effects of two important modulators of outcome expectations (i.e., personalization and personal contact) and, importantly, their temporal dynamics and interaction with person- and depression-related factors.

The objectives are:To determine whether framing the IMI as personalized enhances initial expectations and amplifies treatment effects compared to standard framing.To determine whether expectation-optimizing personal contact amplifies treatment effects. Here, we will also disentangle whether this effect is due to the specific quality of this contact or the non-specific, “common” factors of personal contact by comparing the expectation-optimizing contact to non-specific contact and no-contact conditions.To explore which variables moderate (e.g., do patients with low expectations benefit more from an expectation-optimizing personal contact?) and/or mediate (e.g., therapeutic alliance, self-efficacy) the effects of the expectation-optimizing strategies.To investigate the trajectories of depression, positive and negative expectations, and other relevant treatment factors over time.

### Trial design {8}

The proof-of-concept study uses a 2 (intervention framing pre-treatment: simulated personalization vs. standard framing) × 3 (telephone contact mid-treatment: no contact vs. non-specific contact vs. expectation-optimizing contact) factorial randomized design. Participants will be randomized to one of six intervention arms in a 1:1:1:1:1:1 allocation ratio using block randomization. This study will inspect the effects of (1) experimentally manipulating personalization expectations, as well as (2) personal contact mid-treatment, on depression and participant behavior (adherence and treatment usage).

## Methods: participants, interventions, and outcomes

### Study setting {9}

The study is jointly conducted by Freie Universität Berlin, Germany (FUB) and Philipps-University Marburg, Germany (PUM) and is part of the Collaborative Research Center (CRC)/Transregio 289 “Treatment Expectation”. The CRC 289 is an interdisciplinary collaboration project examining the impact of patient expectations on the efficacy of medical and psychological treatments. Within the present study, the intervention and all assessments will be conducted through the digital research infrastructure DIRECT. DIRECT was developed by the FUB Center for Mental Health and Digital Science as a secure environment for delivering and evaluating IMIs in clinical psychology. Interested individuals can download the DIRECT app on their smartphones to take part in the intervention and data collection. Participants will be self-selected and recruited through advertisements on social media, online media outlets, and patient advocacy networks.

### Eligibility criteria {10}

Individuals will be eligible for participation if they have a depression score indicative of a current depressive disorder, i.e., a BDI-II score ≥ 14 [15]; are ≥ 18 years old; have internet access through a smartphone; live in Germany; and are fluent in the German language. Participants will be excluded if (1) they are currently undergoing psychotherapy or will start psychotherapy within the upcoming three months; (2) report current suicidal ideation (suicidality item of the BDI-II is scored ≥ 2); (3) report current psychotic symptoms (≥ 3 questions of the DIPS psychosis screening rates as “present” [16]); (4) have had a change in psychotropic antidepressant medication within the four weeks before baseline; or (5) are medicated with benzodiazepines. The four-week window reflects the typical adjustment period following initiation or modification of antidepressant treatment, during which short-term symptom fluctuations and side effects may occur. Stabilizing medication for at least four weeks reduces potential confounding effects on depressive symptoms at baseline and during the study. Benzodiazepines will be excluded due to their acute psychotropic effects on depressive symptoms which may influence intervention effects and participants’ self-report.

### Who will take informed consent? {26a}

Participants will provide electronic informed consent within the DIRECT smartphone app.

### Additional consent provisions for collection and use of participant data and biological specimens {26b}

No biological specimens will be collected. By providing consent to participation in the present study, participants will also agree that their data may be analyzed as part of the overarching evaluation of CRC 289. Parts of the data may be shared and analyzed in combination with other subprojects of the CRC. Participants are also asked to consent to data sharing of de-identified data on a repository.

## Interventions

### Explanation for the choice of comparators {6b}

This 2 (intervention framing pre-treatment: simulated personalization vs. standard framing) × 3 (telephone contact mid-treatment: no contact vs. non-specific contact vs. expectation-optimizing contact) factorial randomized controlled trial will examine two randomization factors (framing pre-treatment and personal contact mid-treatment). The comparison is conducted between the treatment arms, considering the potential interaction between the treatment factors.

The first randomization factor concerns the framing of the intervention: Patients will either receive the intervention in the standard framing or receive the same intervention with a personalized framing, simulating that the intervention is tailored to them according to their baseline data. The second randomization factor concerns a personal contact at mid-treatment: Patients will either receive a personal contact session focused on expectations, a supportive personal contact session not focused on expectations, or no personal contact. Thus, we will determine whether modulating outcome expectations by simulating personalization and personal contact at mid-treatment contributes to the treatment outcome at 3, 6, and 12 weeks after randomization.

### Intervention description {11a}

#### IMI

All participants will receive the same IMI. The IMI utilizes established online modules that have proven effective in several large RCTs [17–19]. The IMI comprises six modules that incorporate evidence-based CBT techniques, such as expressive writing, behavioral activation, and cognitive restructuring. The IMI is not guided but contains a messaging button through which participants can reach out with a message in case of questions or technical issues. The content of each module is summarized in Table 1. We recommend a specific dosage (e.g., work ten minutes per day with the daily planner or plan one positive activity per day), but participants themselves decide how to use the provided treatment material. Participants in all treatment arms will get access to the same treatment modules.

**Table 1 Tab1:** Content of each module

**General structure**
The general structure of each module is similar: Participants (1) receive standardized automatic feedback on their work with the previous module, (2) are provided with multimedia educational content on specific depressive symptoms or therapeutic techniques, and (3) are given an exercise to be completed within the module. (4) In modules 3, 4, 5 and 6 participants additionally receive an exercise to be completed daily during the following seven days (e.g., plan one positive activity per day with the planner). Between module 1, 2 and 3 participiants are given a break of three days between modules, after module 3 the break expands to seven days, offering participants enough time to practice their daily exercises
**Module 1: Expressive Writing I: Focusing on the Past**
• Psychoeducation: Depressive Symptoms (e.g., sadness, insomnia, exhaustion) • Exercise: Expressive Writing (~45 min). Participants write a letter reflecting on the circumstances surrounding the onset of their symptoms. Participants are also encouraged to reflect on coping mechanisms and strategies they used so far
**Module 2: Expressive Writing II: Focusing on the Present**
• Psychoeducation: Secondary depressive symptoms (e.g., isolation, overwhelm). Setting realistic goals • Exercise 1: Expressive Writing (~30 min). Participants write a letter reflecting on their current life situation, stressors, and depressive symptoms. Participants are also encouraged to reflect on joyful activities and ressources • Exercise 2: Goals (~30 min). Participans create a list with realistic goals they wish to achieve during the program. Participants are also asked to identify three goals that are most important to them
**Module 3: Behavioral Activation I**
• Psychoeducation: Associtation between activity and mood • Exercise 1: Collection of meaningful activities (~15 min). Participans create a list with activities that are meaningful to them • Exercise 2: Daily Planner and mood tracking (~10 min). Participants are introduced to the integrated daily planner and mood tracking. Participants are encouraged to implement one meaningful activity per day for the following seven days as well as track their mood
**Module 4: Behavioral Activation II**
• Psychoeducation: Coping planning • Exercise 1: Collection of personal barriers and coping strategies (~15 min). Participans reflect on personal barriers obstructing the implementation of meaningful activities. Participants are offered coping strategies to facilitate implementation • Exercise 2: Daily Planner with coping stegies (~10 min). Participants are encouraged to continue their work with the daily planner for the following seven days. Participants are also instructed to reflect on potential barriers while planning and to use coping stragies
**Module 5: Cognitive Reconstructuring I**
• Psychoeducation: Association between cognitions and mood • Exercise 1: Multimedia bias training (~25 min). Participants receive short sequences (video, audio or text) of ambiguous situations. Then, they are presented with three different possible cognitions (either positive, negative, or neutral), of which they choose the one most relable to them. Then, the outcome of the situation is revealed. Inbetween rating situations, participants are educated on specific cognitive biases. In the end, the app provides an automated summary and feedback, revealing either a positive, negative, or neutral bias of the particiants’ cognitions • Exercise 2: Thought record (~10 min). Participants are introduced to the integrated thought record, including (a) situation, (b) thoughts, and (c) feelings. Partipants are instructed to record their thoughts and feelings for the following seven days, especially whenever they feel emotionally activated
**Module 6: Cognitive Reconstructuring II**
• Psychoeducation: Association between alternative cognitions and mood • Exercise 1: Multimedia bias training (~30 min). Participants receive short sequences (video, audio or text) of ambiguous situations. Then, they are presented with three different possible cognitions (either positive, negative or neutral), of which they choose the one most relable to them. Then, the outcome of the situation is revealed. Inbetween rating situations, participants are educated on specific cognitive biases. In the end, the app provides an automated summary and feedback, revealing either a positive, negative or neutral bias of the particiants cognitions • Exercise 2: Extended thought record (~10 min). Participants are introduced to the extended integrated thought record, including (a) situation, (b) thoughts, (c) feelings, (d) alternative thoughts and (d) alternative feelings. Partipants are instructed to use the extended thought record for the following seven days, especially whenever they feel emotionally activated
**Module 7: Expressive Writing III: Focusing on the future**
• Psychoeducation: Relapse prevention • Exercise 1: Warning signs (~10 min). Participans create a list with their personal warning signs indicating the potential onset of a depressive episode • Exercise 2: Expressive writing (~20 min). Participants write a letter reflecting on their symptoms and feelings in the beginning of the program. Participants are also encouraged to reflect on their achievements, symptom improvement as well as coping stragies they learned during the program

The IMI utilizes modules that have been investigated in several large RCTs [17–19]

#### Personalization expectation

With the first randomization factor (2 levels), we aim to modulate expectations by simulating a personalized IMI. Participants in the “personalized” arm will receive a sham version of the IMI that they believe is tailored to their needs based on their baseline data (although it is the same intervention as in the comparison group). Specifically, participants will be informed that the study team has selected the most suitable intervention components for them. The following measures will be taken to make the simulated personalization salient:Before initiating the first module, participants are informed about the group to which they were randomized. Participants in the personalized group are informed about a personalized selection of the intervention modules based on their previously entered data, as well as the concept and expected benefits of personalized interventions. Participants in the standard group will receive an informative text about receiving the intervention in a previously established version. All of this information is conveyed written in the app.In addition to informing them about their group allocation and the personalized modules, we introduce the metaphor of a “key-lock-principle.” The standard group will receive no further specification through means of a metaphor.For the personalized group, the picture of a key will be displayed visually along with the CBT exercises in each of the six modules to make the “key-lock-principle” salient. In the standard group, we will display a generic picture of a thought bubble (see 4. below).Within each module, we will tailor the headline of the psychoeducation of the respective exercise to the allocated group. While it will read “Why am I doing this?” in the standard group, the personalized group will read the headline “Why was this selected for me?”. The provided informative text about the relevance of the exercise will be the same for both groups.Finally, after each module, we will assess how participants perceived the fit of the session to their needs (“session fit”). Thus, we expect to increase participants’ perception that the intervention is indeed personalized by creating the impression of asking about the efficacy of an underlying matching procedure. For the standard group, we will ask the same question. Since we did not introduce an adaption for this group, we expect that group to perceive the question about the “session fit” as a routine form of evaluation.

#### Personal contact mid-treatment

With the second randomization factor, we will investigate the effects of different variants of personal contact mid-treatment. Participants will either receive (1) no personal contact via telephone or a phone contact that is (2) supportive without focusing on expectations or (3) expectation-optimizing. The (2) non-specific telephone calls are exclusively supportive, without touching upon expectations. Thus, the supportive contact will not have a specific topic. Instead, participants are free to share any topic or concern. The telephone counselors will be trained to respond in a non-directive, empathetic manner. However, they are instructed to avoid any interventions, including interventions that may target expectations. In the (3) expectation-optimizing contact, the phone contact will focus on the expectations of the participants. The participants will be asked about their previous experiences with the intervention and about what they expect to change until the end of the intervention. The phone counselors will be trained to analyze participant’s expectations, enhance positive and realistic expectations, and modify maladaptive or unrealistic expectations by using interventions that are useful in optimizing expectations [20], including psychoeducation, informing about the effectiveness of the interventions, or increasing participants’ sense of control, in a warm and competent manner. The non-content-related aspects of the personal contact in conditions (2) and (3) are parallelized between the arms. The duration of the telephone contacts are planned to be 20 to 30 min. Counselors are master students of clinical psychology/psychotherapy who demonstrate psychotherapeutic relationship skills (e.g., empathic listening, validation). They will receive comprehensive training before treating the first client (see Section “Strategies to improve adherence to interventions {11c}”) to ensure that the intervention is delivered in a consistent manner across all participants.

### Criteria for discontinuing or modifying allocated interventions {11b}

Participants can discontinue their study participation at any time without any consequences. If a participant stops working with the IMI, they will nevertheless be invited to complete the scientific assessments. Participants will not be reallocated to another intervention arm. Moreover, the intervention will not be modified at any stage by the study team. However, it is possible that participants in one of the two personal contact groups may not complete the mid-treatment intervention (e.g., due to organizational issues). In this case, they will receive written information and questions in the app, either in a purely supportive or expectation-optimizing manner.

### Strategies to improve adherence to interventions {11c}

#### Adherence of telephone counselors

To enhance comparability and ensure adherence to the intervention protocol and the delivery of the personal contact intervention, we have implemented several measures: (1) each telephone counselor will be trained to conduct either the expectation-optimizing or non-specific, supportive telephone calls, (2) all counselors receive a talk schedule, (3) the first 2 (more if necessary) telephone calls conducted by each counselor will be carried out jointly with the supervisor. Moreover, (4) the next 2–3 conducted calls will be rated for fidelity by an external observer. In case of insufficient fidelity, telephone counselors will receive additional, targeted training as determined on a case-by-case basis by the supervisor. (5) After this training period, telephone counselors will conduct calls independently under weekly supervision. A psychotherapist with extensive expertise in IMIs will train and supervise counselors.

During the intervention phase, 10–20% of phone calls will be audio-recorded and evaluated for fidelity to the core principles by an external observer.

For the fidelity ratings, a study-specific measure was developed based on established fidelity scales [21, 22] and adapted to the specific requirements of the telephone calls in this study. Participants receiving the contact mid-treatment will also be asked, after the phone call, to indicate in one open-ended question what the contact was about. Telephone counselors will also rate how they adhered to the talk schedule.

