### Sample size {14}

To depict a clinically meaningful effect size of *d* = 0.35 between two arbitrary cells (e.g., personalized framing and expectation-optimizing contact vs. standard framing and no contact) in this proof-of-concept study, with an alpha of 0.05 and power of 0.80 (one-tailed, uncontrolled for multiplicity), an overall sample size of approximately 200 is needed according to G*Power [14]. The resulting sample of *N* = 600 (*n* = 100 per cell) should be sufficiently large to depict trends and inform future confirmatory trials. To consider a dropout rate of 20% per arm, we aim to recruit *N* = 720 patients (120 per treatment arm). We will include data assessed before starting the intervention as covariates to increase power.

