## Statistical methods

### Statistical methods for primary and secondary outcomes {20a}

The planned analysis is described below. We will publish an updated statistical analysis plan before analyzing the research report for research question 1. This plan will take into account any issues that cannot be predicted at this stage but may emerge during the conduct of the trials (e.g., higher rates of people not receiving the intervention as planned).

Main Research Question 1: *How do simulated personalization before treatment and expectation-optimized personal contact 3 weeks after treatment initiation modulate treatment effects (e.g., the difference in depressive symptom load and secondary outcome measures at 3, 6, and 12 weeks after randomization) and treatment discontinuation?*

We assess the differences in depressive symptom load 3, 6, and 12 weeks after randomization. We treat the BDI-II score as a continuous variable. We will use factorial ANCOVA models. To explore the difference in depressive symptoms 3 weeks after treatment initiation, we use simulated personalization (F1) as the independent variable. For week 6 and 12, we use mid-treatment expectations focused contact (F2), as well as the interaction between F1 and F2 as independent variables. All ANCOVA models will include age and baseline symptom severity as covariates. We will report marginal means for each factor level of the main factors and means for each treatment arm. Pairwise comparisons between factor levels corrected for multiplicity will be reported. We will apply the same method for all other continuous secondary outcome measures available at the respective measurement occasions. We will report the difference in means in units of the scale score. Cohen’s *d*-like effect sizes will be reported. Effects on treatment discontinuation will be inspected using a rank-based test for factorial designs. Differences in rates, as well as relative effects, will be reported.

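### Counselors are nested within call type, but the week 6 and 12 contact contrasts use an ANCOVA that assumes independent participants; if outcomes vary by counselor, the standard errors are too small

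*Protocol article*

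**What the plan says.** Under Adherence of telephone counselors {11c}, the protocol article says that "each telephone counselor will be trained to conduct either the expectation-optimizing or non-specific, supportive telephone calls". The natural reading is that a counselor delivers only one call type. The same section has each counselor make several calls: the first 2 jointly with the supervisor, the next 2 to 3 rated for fidelity, then further calls independently. Personal contact mid-treatment adds that "Counselors are master students of clinical psychology/psychotherapy who demonstrate psychotherapeutic relationship skills".

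Statistical methods {20a} states: "We will use factorial ANCOVA models". For weeks 6 and 12 it names the contact factor F2 and the F1×F2 interaction as independent variables. Age and baseline severity are covariates, and the pairwise comparisons are corrected for multiplicity. The article contains no counselor term, mixed model or cluster-robust standard error.

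Sample size {14} works from independent observations: "an overall sample size of approximately 200 is needed according to G*Power" for two cells. It includes no design effect.

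**The concern.** Participants called by the same counselor share whatever that counselor brings to the call. Both call levels are clustered in this way and the no-contact level is not, which makes the design partially nested. An ANCOVA on individual participants leaves between-counselor variance out of the standard error. No counselor appears in both call types, so that variance passes straight into the difference between them.

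The contrast most exposed is the one behind the second objective, which asks whether an effect comes from the expectation content or from personal contact as such. The Strengths and limitations section presents the supportive call as a key strength for this reason. A chance difference between two sets of student counselors could be reported as an effect of call content.

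The protocol's own rationale makes counselor differences plausible. The Background argues that information changes negative expectations when it is given warmly and competently, and not otherwise. The plan also measures the counselor's warmth and competence after the call.

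**Working it through.** **Inputs from the article.** Standardised effect 0.35 between two cells, one-tailed alpha 0.05, power 0.80; 100 analysed per cell, hence 2 × 100 = 200 per F2 level; equal allocation to six arms; one call type per counselor; ANCOVA without a counselor term.

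**Inputs assumed, because the article does not give them.** Counselors per call type K = 5 to 40; ICC of the outcome by counselor 0.01 to 0.05; share of calls delivered 100% or 70%.

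**Step 1: the plan's own figure.** n per cell = 2(1.645 + 0.842)² / 0.35² = 100.9, so 101 per cell and 202 in total. The exact noncentral t gives 102 per cell and 204 in total. The stated figure of about 200 is reproduced, and it rests on independent observations.

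**Step 2: expectation-optimizing versus supportive call, all calls delivered.** With m = 200/K participants per counselor, the design effect is DE = 1 + (m − 1) × ICC. The true standard error is √DE times the ANCOVA one, so the true two-sided alpha is 2 × [1 − Φ(1.96/√DE)].

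- K = 5, ICC 0.05: m = 40, DE = 1 + 39 × 0.05 = 2.95, √DE = 1.72, alpha 0.254.
- K = 40, ICC 0.01: m = 5, DE = 1 + 4 × 0.01 = 1.04, √DE = 1.02, alpha 0.055.

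| K per call type | ICC 0.01 | ICC 0.02 | ICC 0.05 |
|---|---|---|---|
| 5 | 0.096 | 0.142 | 0.254 |
| 10 | 0.072 | 0.095 | 0.160 |
| 20 | 0.060 | 0.071 | 0.104 |
| 40 | 0.055 | 0.059 | 0.074 |

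**Step 3: check by simulation of the 2×3 ANCOVA** (100 per cell, counselors nested in F2 and crossed with F1, 4,000 runs, no true effect). Rejection rates were 0.052 at ICC 0; 0.076, 0.095 and 0.165 for K = 10 at ICC 0.01, 0.02 and 0.05; 0.270 for K = 5 and 0.105 for K = 20, both at ICC 0.05. These agree with the formula.

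**Step 4: call versus no contact.** Only one side is clustered, so the variance ratio is (DE + 1)/2. For K = 10 this is (1.38 + 1)/2 = 1.19 at ICC 0.02 and (1.95 + 1)/2 = 1.475 at ICC 0.05. The true alpha is 0.072 and 0.107 (simulated 0.072 and 0.115).

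**Step 5: 70% of calls delivered, K = 10.** The simulated alpha for expectation versus support is 0.066 at ICC 0.02 and 0.117 at ICC 0.05. As a cross-check, 140 called participants per level give 14 per counselor, so the variance ratio is 1 + (140 × 13/200) × ICC. That is 1.182 and 1.455, or alpha 0.071 and 0.104. The two methods differ by 0.5 and 1.3 percentage points; the simulation's standard error is about 0.4 to 0.5 points.

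**Step 6: what is not affected.** With counselors serving both framing groups, the F1 main effect and the F1×F2 interaction rejected at about 0.04 to 0.06. The week 3 model contains F1 only.

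**The case against.** The strongest reply is that the inflation depends wholly on an ICC that the article does not give. The contact is one call of 20 to 30 minutes within a six-week unguided program. Non-content aspects are parallelized between the two call types. Talk schedules, joint first calls, fidelity ratings, retraining, weekly supervision and audio checks on 10–20% of calls all aim to make counselors alike. Missed calls are replaced by written in-app content, and those participants have no counselor. The trial is a proof-of-concept, and an updated analysis plan is announced.

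Much of this stands, and it bears on size and severity. A reader might infer that the standard errors are certainly too small, that the false-positive rate is near the top of the range, or that the whole factorial analysis is invalid. The documents support none of these. At ICC 0 there is no inflation, and measuring warmth and competence does not show that outcomes differ by counselor. The top of the range needs few counselors, a high ICC and full delivery together. The figures are also for a nominal 5% test, whereas the planned pairwise tests are corrected for multiplicity, so they are not the rates at which the planned contrast would be declared positive.

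Three parts of the reply fail. Training may shrink counselor variance but does not put the remainder into the standard error. Multiplicity correction does not repair a standard error that is too small. The updated plan is reserved in {20a} for issues that cannot be predicted at this stage, whereas the nesting is a design decision already made and the model terms are already named. This is therefore not a detail left to an unseen analysis plan.

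**Conclusion.** The concern holds in conditional form. The nesting and the absence of a counselor term follow from the text; the size of the effect on inference does not. If outcomes vary by counselor, the week 6 and 12 F2 standard errors are too small, most for expectation-optimizing versus supportive call and less for call versus no contact.

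With 5 to 40 counselors per type, ICC 0.01 to 0.05 and all calls delivered, a nominal 5% test of expectation versus support has a true type I error of about 5.5% to 27%. With 10 counselors per type, 70% delivered and ICC 0.02 to 0.05, it is about 6.6% to 11.7%. The F1, F1×F2 and week 3 results are unaffected provided counselors serve both framing groups, which the article does not state.

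This should be fixed. It falls short of a fatal flaw, because the trial is meant to show trends and the remedy needs no change of design.

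**What to change.** Record the counselor ID for every delivered call. Analyse the week 6 and 12 F2 effects with a partially nested mixed ANCOVA: a random counselor intercept in the two call levels, no-contact and never-called participants as singletons, and Satterthwaite or Kenward-Roger degrees of freedom. Fixed counselor effects will not serve, because they are confounded with call type.

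The main analysis under {20c} uses multiple imputation, so the imputation model should reflect the counselor structure and the plan should state a degrees-of-freedom rule for the pooled estimates. Report the number of counselors and the ICC, and say plainly that counselor and call content cannot be fully separated when no counselor delivers both.

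The cost is one exported variable, revised analysis wording, some added work on the imputation, and wider F2 intervals. For scale, with 10 counselors per type, all calls delivered and a two-sided t-test on 2K − 2 = 18 degrees of freedom, power for a difference of 0.35 between the two call types is 0.91, 0.86, 0.80 and 0.66 at ICC 0, 0.01, 0.02 and 0.05. Recruitment is expected to run to mid-2027, so the variable can still be captured.
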